#### Procedure for unblinding if needed {17b}

It is an open-label study and therefore unblinding will not occur.

## Data collection and management

### Plans for assessment and collection of outcomes {18a}

During the registration process, contact data of all interested individuals are collected. The data are deleted if the person disagrees to participate in the study or does not meet the criteria.

All parameters as described in the subsection ‘Outcomes (see {12})’ are taken in a group testing setting with appropriate COVID-19 safety measures, e.g. testing, vaccination, hygiene procedures by the staff of the St. Pölten University of Applied Sciences either at the university itself or at David Institute Krems.

Due to the need for blood sampling and anthropometric measurements at T0, T2, T3 and T4, data collection is conducted in the morning in a fasting state. Anthropometric measurements are conducted with light clothing and carried out by dietitians and nutritionists.

The functional tests (40 MFPWT and 30 SCST) are also carried out with light and casual clothing as well as shoes after the anthropometric measurements. A fasting state is not necessary. Demographic and anamnestic data as well as quality-of-life parameters (KOOS and EQ-5D-5L) are collected via online questionnaires using LimeSurvey (https://www.limesurvey.org/de) as online survey tool. For the data entry, the participants use prepared laptops at the measurement site. Blood samples are collected by medical staff from the David Institute. Fresh blood samples are centrifuged and processed according to the specifications of each biochemical parameter (see ‘Outcomes {12}’) at the University of Continuing Education Krems (located in close proximity to the David Institute). All processed blood samples are stored at − 80 °C and analysed at the University of Continuing Education Krems and at the University of Vienna.

Besides this data collection at the measurement appointments, 24-h dietary recalls are conducted as described in Outcomes ({12}).

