### Criteria for discontinuing or modifying allocated interventions {11b}

Participants can revoke their willingness to participate at any time, even without giving reasons, and withdraw from the clinical study without any disadvantages for their further medical care.

The principal investigator may terminate a participation in the study prematurely without obtaining the participants' consent beforehand. Reasons for this include:

Participants do not longer meet the inclusion criteria of the clinical study.The treating physician comes to the conclusion that continued participation in the clinical study is not in the participants' best interest.The study coordinator decides to terminate the entire clinical study, or to terminate only one subject’s participation prematurely.

Furthermore, participants must attend at least three out of four dietetic group training sessions and eight out of twelve GLA:D® training programme sessions. If a participant cannot meet this quota, he/she is excluded from the study.

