### Outcomes {12}

Data are collected five times over a period of 12 months: at baseline (T0), 6 weeks after the start of the intervention (T1; T0 + 6 weeks), 3 months after the start of the intervention (T2; T0 + 3 months), 9 months after the start of the intervention (T3; T0 + 9 months) and after the follow-up period (T4; T0 + 12 months), including the assessment of blood-based biochemical, anthropometric and behavioural parameters at four data collection points (T0, T2, T3 and T4). The collection of demographic and anamnestic data and the execution of the functional tests take place at all five data collection points.

The primary outcome is the quality of life subscale (QL) of the Knee Injury and Osteoarthritis Outcome Score (KOOS) [62]. The KOOS is used to assess the joint function and patients’ opinion about their knee and associated problems and is a valid and reliable tool compared to others in several studies [62]. The KOOS score for knee-related quality of life (QL) is one of five subscales of the KOOS questionnaire. The QL score is calculated based on four 5-point Likert scale questions, in which each question is assigned a score between 0 and 4. According to the standardised score calculation (www.koos.nu), the mean of the observed items is divided by 4, multiplied by 100 and finally subtracted from 100. A QL score of 100 indicates no symptoms, while a score of 0 means extreme symptoms. The KOOS is valid and reliable and was compared to other instruments in several studies [62].

To evaluate the symptoms of the knee OA and associated problems, the following parameters are analysed:

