### Plans to promote participant retention and complete follow-up {18b}

As with the other measurement time points, participants receive a reminder for the follow-up appointment. After the last measurement, the financial compensation is paid and the participants receive their personal test results. In addition, the members of the control group then have the possibility to consult the dietitian.

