### Data management {19}

The participants agree that for the purpose and in the course of this study, the St. Pölten University of Applied Sciences collects and processes behavioural, anthropometric, demographic and anamnestic data as well as data from the KOOS and functional tests (see ‘Outcomes {12}’). Furthermore, the participants agree that the University of Continuing Education Krems and the University of Vienna transmit the biochemical data (see ‘Outcomes {12}’) in pseudonymised form to the St. Pölten University of Applied Sciences.

The participants’ data are pseudonymised and assigned a fixed identification code. This code is stored safely in a password-protected file, accessible only by the study coordinator (BW) and central staff members (SC, TA, EH). Thus, it is only possible for persons who are entrusted with the evaluation of the data to infer the identity of the participants.

Data acquisition and data processing are performed using commercial software. All data obtained are stored in computer files in encrypted form at the server of the St. Pölten University of Applied Sciences. The handling of the data complies with the European General Data Protection Regulation, the Austrian Data Protection Act and the recommendations of the Austrian Ethics Committees.

Quantitative data are stored and analysed via the statistical software package SPSS at servers of the St. Pölten University of Applied Sciences. To be able to merge the data from the online questionnaires, anthropometric measurements and the blood sample data, a defined coding system is used. Therefore, central staff members (SC, TA) take part in every measurement and organise the participants and coding system. Hence, every participant gets their identification code for the anthropometric measurements and the blood samples and a personalised link including password for the online questionnaire via *Limesurvey*. The identification code ensures that the study staff do not know to which group each participant belongs. To support participants in completing the online questionnaires, prepared laptops and supporting staff members are available. The questionnaires are checked on site by the study staff in terms of completeness and correctness related to the specifications of the questionnaires. Study data from online questionnaires are exported and saved as a comma-separated values (CSV) file after every measurement.

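### The only route described for KOOS-QL is a laptop at the measurement appointment, with no fallback for a missed visit, so obtainable T4 answers may be left to imputation

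*Protocol article*

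**What the plan says.** Outcomes {12} names the KOOS quality of life subscale, scored from four Likert items, as the primary outcome. Statistical methods {20a} puts the focus on T0 against T4 (12 months).

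Plans for assessment and collection of outcomes {18a} says that all outcome parameters "are taken in a group testing setting with appropriate COVID-19 safety measures" at the university or the David Institute. It adds that "quality-of-life parameters (KOOS and EQ-5D-5L) are collected via online questionnaires using LimeSurvey", and then: "For the data entry, the participants use prepared laptops at the measurement site". Where blood and anthropometry are due, including T4, data collection takes place in the morning with participants fasting.

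Data management {19} gives each participant "a personalised link including password for the online questionnaire". It describes the laptops and staff as support, and has the questionnaires checked on site.

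Plans to promote participant retention and complete follow-up {18b} reads: "As with the other measurement time points, participants receive a reminder for the follow-up appointment". Payment, personal results and, for controls, access to the dietitian follow the last measurement.

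Criteria for discontinuing or modifying allocated interventions {11b} lets participants "withdraw from the clinical study without any disadvantages for their further medical care", lets the investigator end a participation, and excludes anyone below the attendance quota (three of four dietetic sessions, eight of twelve GLA:D sessions). Section {20c} plans intention to treat for non-adherence and multiple imputation for missing data.

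**The concern.** Nothing in four self-report items needs a site visit, a fasting morning or a blood draw. Yet the only collection route described for them is the appointment that includes all of these. The section meant to secure complete follow-up offers a reminder and end-of-study incentives, but no second route to the primary endpoint. The discontinuation section describes no status for a person who has stopped the intervention and still answers the questionnaire.

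At stake is the completeness of the T4 comparison. Intention to treat needs outcomes from people who did not adhere. In a diet trial, those who miss the last visit may differ from those who attend, and imputation then rests on an assumption that an observed answer would not need. The loss could also differ between arms, because only the intervention group receives the dietetic sessions to which part of the quota applies.

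**Working it through.** **What the sections give when set side by side**

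| Question | Answer in the protocol |
|---|---|
| Can KOOS be answered away from the site? | Technically yes: online tool, personal link with password ({18a}, {19}) |
| Is off-site completion described? | No. The described route is a laptop at the measurement site ({18a}) |
| Is it forbidden? | No. {19} calls the laptops support |
| Is there a fallback for a missed visit? | None stated in {18a}, {18b} or {19} |
| Is remote contact used elsewhere? | Yes: telephone dietary recalls ({12}), telephone or virtual counselling ({11a}), online first appointment ({26a}) |
| Is there a status between full participation and leaving? | None described in {11b} |
| Does the analysis need outcomes from non-adherers? | Yes: intention to treat ({20c}) |

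**Illustration of size**

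Inputs from Sample size {14}: 50 required, 20% drop-out, 60 enrolled, SD 15, minimally important change 8–10 points. The documents give no rate of missed visits.

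1. The plan's own figure: 50 × 1.20 = 60.
2. Expected loss: 0.20 × 60 = 12. Observed at T4: 60 − 12 = 48, or 24 per arm.
3. Assumption: half of the 12 answer by link. Observed: 48 + 6 = 54, or 27 per arm.
4. Standard error of a difference in means = SD × √(2/n). With 24 per arm: 15 × √(2/24) = 4.33 points. With 27 per arm: 15 × √(2/27) = 4.08 points. Ratio: √(48/54) = 0.943, a fall of about 6%.
5. Power of a two-sided 5% t-test for a 10-point difference with SD 15: 61.8% with 24 per arm and 67.2% with 27 per arm. For the protocol's effect size of 1.1, read as a standardised difference, it is 96.2% and 97.8%.
6. Bias in one arm's mean = proportion missing × the difference between lost and retained that imputation fails to capture. With 20% missing, each uncaptured point shifts the mean by 0.2 point. If that difference were 5 to 15 points (an assumption with no source in the documents), the shift is 0.20 × 5 = 1 to 0.20 × 15 = 3 points. This is 1/10 = 10% to 3/8 = 37.5% of the minimally important change.

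Steps 3 to 5 compare observed cases only. Imputation that draws on earlier KOOS scores would already recover part of this information, so the real gain in precision is probably smaller.

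**The case against.** The case against is substantial, and most of it limits the point.

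- **The text does not say that KOOS can be completed only on site.** A reader might infer a prohibition. The documents do not support that: the laptops are described as support, and nothing bars use of the link elsewhere.
- **Stopping the diet does not prevent attendance.** A reader might infer that everyone who stops loses KOOS-QL at T3 and T4, or that stopping one component counts as withdrawal. Section {11b} says neither. It grants a right to leave the study and is silent on partial stopping.
- **For people below the attendance quota, the exclusion rule causes the loss.** A link alone would not recover them.
- **Retention is broader than {18b}.** Section {11c} adds text reminders a week ahead, time slots, close contact with the dietitian, interim results, a goodie bag and free physiotherapy. Payment is not made conditional on adherence, so it needs no change.
- **The 20% covers all drop-out.** It may include people who withdraw all consent, whom a link could not reach. Similar loss in both arms would largely cancel in the contrast. If responders to the link are themselves selected, recovering half of the answers does not halve the bias.
- **On-site completion has merits:** a completeness check, staff help and uniform conditions.
- **An article may leave a missed-visit procedure to the full protocol.**

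The last objection does not dispose of the point, because the article does state a collection procedure and a follow-up plan. The point is that a better procedure is available with tools already in place, not merely that a detail is absent.

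**Conclusion.** The point holds as a cheap improvement to a stated procedure, not as an error. The only described route to a web-based, self-reported primary endpoint is a site visit; no fallback is stated; and the discontinuation section describes only leaving or exclusion, while the analysis promises intention to treat. Some T4 answers that could be obtained may therefore be imputed instead.

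The size is modest and illustrative: 54 rather than 48 observed, and a standard error about 6% lower, if half of the planned drop-outs answered. The 1 to 3 points of bias in one arm's mean rest on an assumed difference and on imputation capturing none of it. They show why observed answers are preferable and are not an estimate for this trial.

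**What to change.** 1. In {18a} and {18b}, keep on-site completion as the default. For anyone who misses or declines an appointment and has not withdrawn consent for data, send the existing personal LimeSurvey link for KOOS and EQ-5D-5L, with one reminder. Record the place of completion in the dataset.
2. In {11b}, distinguish stopping the intervention, including falling below the attendance quota, from withdrawing consent for data, so that outcome collection continues in the first case as {20c} requires. This concerns data collection only; the quota itself is not at issue here.

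**Cost:** no new staff or infrastructure. Section {25} requires approval from the ethics committee and the funder, and re-consent if the change differs significantly from what participants were told. Remote forms lose the on-site completeness check, which mandatory items can partly replace. They also introduce a small mode difference, which the flag allows to be examined. Recruitment ended in January 2024, so the change helps only visits still outstanding.

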### Plans to promote participant retention and complete follow-up {18b}

As with the other measurement time points, participants receive a reminder for the follow-up appointment. After the last measurement, the financial compensation is paid and the participants receive their personal test results. In addition, the members of the control group then have the possibility to consult the dietitian.

### Data management {19}

The participants agree that for the purpose and in the course of this study, the St. Pölten University of Applied Sciences collects and processes behavioural, anthropometric, demographic and anamnestic data as well as data from the KOOS and functional tests (see ‘Outcomes {12}’). Furthermore, the participants agree that the University of Continuing Education Krems and the University of Vienna transmit the biochemical data (see ‘Outcomes {12}’) in pseudonymised form to the St. Pölten University of Applied Sciences.

The participants’ data are pseudonymised and assigned a fixed identification code. This code is stored safely in a password-protected file, accessible only by the study coordinator (BW) and central staff members (SC, TA, EH). Thus, it is only possible for persons who are entrusted with the evaluation of the data to infer the identity of the participants.

Data acquisition and data processing are performed using commercial software. All data obtained are stored in computer files in encrypted form at the server of the St. Pölten University of Applied Sciences. The handling of the data complies with the European General Data Protection Regulation, the Austrian Data Protection Act and the recommendations of the Austrian Ethics Committees.

Quantitative data are stored and analysed via the statistical software package SPSS at servers of the St. Pölten University of Applied Sciences. To be able to merge the data from the online questionnaires, anthropometric measurements and the blood sample data, a defined coding system is used. Therefore, central staff members (SC, TA) take part in every measurement and organise the participants and coding system. Hence, every participant gets their identification code for the anthropometric measurements and the blood samples and a personalised link including password for the online questionnaire via *Limesurvey*. The identification code ensures that the study staff do not know to which group each participant belongs. To support participants in completing the online questionnaires, prepared laptops and supporting staff members are available. The questionnaires are checked on site by the study staff in terms of completeness and correctness related to the specifications of the questionnaires. Study data from online questionnaires are exported and saved as a comma-separated values (CSV) file after every measurement.

Results of the biochemical analysis are uploaded by the University of Continuing Education Krems and the University of Vienna via encrypted Excel files to a protected research server at the St. Pölten University of Applied Sciences and imported into SPSS by the study coordinator.

Anthropometric data are collected on site using the identification codes in the encrypted and password-protected cloud application of SECA (https://www.seca.com/de_at/555.html). Also, these data are exported and saved as a comma-separated values (CSV) file after every measurement.

Furthermore, the St. Pölten University of Applied Sciences performs data back-ups on a daily basis. All signed informed consent forms as well as all collected pen-and-paper sheets are stored in a locked place, accessible only for the study coordinator and a central staff member (SC). All data are stored at the St. Pölten University of Applied Sciences for 10 years after the study’s end. After that, all data are to be destroyed.

To ensure data quality, the study coordinator controls the data at regular intervals, which includes a check of the range of values or double data entry. Results of all analyses are reported in an aggregated and strictly anonymous form.

### Confidentiality {27}

All collected data are kept confidential as described in ‘Data management’ (see {19}). Only the study coordinator (BW) and central staff members (SC, TA, EH) can open the password-protected file to link personal information and code. The final pseudonymised dataset in SPSS will be used by the study staff for analyses, publications and reports only for this study.

### Plans for collection, laboratory evaluation and storage of biological specimens for genetic or molecular analysis in this trial/future use {33}

Not applicable as no biological specimens for genetic or molecular analysis are collected.

## Statistical methods

### Statistical methods for primary and secondary outcomes {20a}

In this study, the focus is on the comparison of data collected at the beginning of the study (T0) and at the end of the study (T4; T0 + 12 months). For all statistical tests, the significance level is set at *p* < 0.05 in accordance with scientific standards. Data are analysed using IBM SPSS Statistics 28 or greater. Normal distribution of metric variables is tested with Shapiro–Wilk-Test and Q-Q-diagrams. For interpreting the results correctly, we also conduct a descriptive analysis showing the arithmetic mean and standard deviation of metric outcome parameters for each group. To control for outliers, we also report the minimum and maximum for each group in addition to a supportive graphical analysis. For interval and nominal scaled variables, we conduct a frequency analysis. To compare the effects of an evidence-based training programme (GLA:D®) with and without the nutrition therapy Austrian OA Cuisine, we conduct an analysis of variance (ANOVA) based on a mixed-linear model of repeated measures looking for assessing effects within each group (e.g. between baseline and the other data collection points) and between groups. In case variables are non-normal or non-metric in scale, we use the Friedman Test, respectively [83]. The group variable (intervention group or control group) serves as the independent variable and the observed outcome parameters (see {12}) serve as the dependent variable.

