### Objectives {7}

The main objectives of this study are, on the one hand, to analyse the effect of the nutrition therapy Austrian OA Cuisine combined with the GLA:D® training programme on QL in patients with mild to moderate knee OA. On the other hand, the study investigates the impact of a nutrition therapy combined with the GLA:D® training programme on symptoms, nutrition and inflammation status and oxidative stress markers, as well as joint function in patients with mild to moderate knee OA.

In particular, our main hypotheses are

H1: Austrian OA Cuisine combined with the GLA:D® training programme will improve QL in patients with mild to moderate knee OA.H2: Austrian OA Cuisine combined with the GLA:D® training programme will reduce symptoms in patients with mild to moderate knee OA.H3: Austrian OA Cuisine combined with the GLA:D® training programme will improve the nutrition status in patients with mild to moderate knee OA.H4: Austrian OA Cuisine combined with the GLA:D® training programme will improve the inflammation status in patients with mild to moderate knee OA.H5: Austrian OA Cuisine combined with the GLA:D® training programme will improve the oxidative stress markers in patients with mild to moderate knee OA.

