Further KOOS subscales collect the participants' opinion about their knee pain (Pain), knee function in daily living (ADL), knee function in sport and recreation (Sport/Rec) and other knee-associated symptoms (Symptoms). The latter is relevant for testing H2. Equally to the KOOS subscale QL, each subscore is calculated based on 5-point Likert scale questions, where each question is assigned a score from 0 to 4. Following the standard procedure for the subscore calculation, the mean of the subscore questions is divided by 4, multiplied by 100 and finally subtracted from 100. A subscore of 100 indicates no symptoms, while a score of 0 points to extreme symptoms.To evaluate the functional status of the participants' knee, the 40-m fast-paced walk test (40 MFPWT) and the 30-s chair stand test (30 SCST) are performed. The 40 MFPWT is a valid and reliable tool to measure gait speed and to monitor changes in knee OA patients’ physical function over time [63]. The 30 SCST is a valid and reliable tool to measure lower limb strength in patients with knee OA [64].

The following nutritional parameters are used as the basis for testing the third hypothesis:

Anthropometrical parameters:Body height [cm], body weight [kg] and body fat [%] as measured using Seca mBCA 555. The device measures body weight with a scale, body height with ultrasound length measurement and body composition by the voltage drop of the alternating current in one stepWaist circumference [cm] to calculate the waist-to-height ratio as measured using an ergonomic, stepless and extendible measuring tape

Biochemical parameters:Lipide profile (plasma α-linolenic acid, plasma linoleic acid, plasma total polyunsaturated fatty acids, plasma Ω6:Ω3 ratio), measured as described in [65];Carotenoids (α- and β-carotene, lutein, lycopene), measured as described in [66, 67] and;Vitamins D [68] and K, measured as described [66].

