Behavioural parameters:Dietary behaviour is measured using an adapted version of the Vienna Food Record (VFR), which is a paper-based prospective food record and can be completed without an interview or oral instruction. The VFR consists of 182 food items which meet the requirements of Austrian adults [69]. For this study, adaptations to assess fat quality (fat fish, vegetable oils, nuts and seeds) more precisely were implemented. To support participants in answering the VRF, an additional booklet with real portion size pictures corresponding to the food items are provided to the participants.

Additionally, the oxidative stress and inflammatory status are determined as secondary outcomes based on the following biochemical parameters:

Oxidative stress parameters (ferric reducing ability potential, malondialdehyde, oxidised and reduced glutathione, damage to desoxyribonucleic acid), measured as previously described [70].Inflammation biomarkers (C-reactive protein, interleukins (IL)-1β, IL-6, IL-18, tumour necrosis factor alpha, matrix metalloproteinase (MMP)-3), measured by multiplex assays as described previously [71].

In addition to the outcome parameters, the following demographic and anamnestic data are collected:

Sex, gender, employment status, residence, number of people in the household, income, immigration background [72]Consumption of alcohol and smoking behaviourSleep qualityClinical information (menopausal status, regular intake of supplements and drugs, medical history, joint complaints, sick leave)Actual self-perceived health status and painPhysical activity level at work, leisure time activitiesThe general physical activity level is assessed using the ‘International Physical Activity Questionnaire Short Form’ (IPAQ-SF) [73]: The IPAQ-SF asks seven questions to assess ‘vigorous-intensity’ and ‘moderate-intensity’ physical activity as well as ‘walking’ and ‘sitting’. Participants indicate the time in minutes or hours for each activity level. Based on this information, three levels of physical activity (low, moderate, high) are calculated and expressed in the metabolic equivalent of task (MET) minutes per week.Feedback on the participants’ satisfaction with the GLA:D® training programme will be collected at T1 and T4 by using a visual analogue scale.

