### Methods for additional analyses (e.g. subgroup analyses) {20b}

Depending on the data and data distribution, subgroup analyses are carried out, e.g. data is clustered according to the body weight. In addition, different correlations - like between the clinical data and the dietary behaviour of the participants - can be analysed.

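### H3–H5 are labelled main hypotheses and rest on about 13, 6 and 5 markers, each tested at 5%, with no rule for how the markers together decide the hypothesis

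*Protocol article*

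**What the plan says.** Objectives {7} introduces five hypotheses together with "In particular, our main hypotheses are" and gives no order among them. H4, for example, reads "Austrian OA Cuisine combined with the GLA:D® training programme will improve the inflammation status in patients with mild to moderate knee OA". H3 and H5 have the same form for nutrition status and oxidative stress markers.

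Outcomes {12} sets a different ranking: "The primary outcome is the quality of life subscale (QL) of the Knee Injury and Osteoarthritis Outcome Score (KOOS"), and Sample size {14} powers only that subscale. Outcomes {12} also presents oxidative stress and inflammatory status as secondary outcomes.

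For H2 the article picks out one variable. After listing the other KOOS subscales, with Symptoms last, it adds "The latter is relevant for testing H2". For H3 it gives a list of anthropometric, biochemical and dietary parameters as the basis of the test. The inflammation list is "Inflammation biomarkers (C-reactive protein, interleukins (IL)-1β, IL-6, IL-18, tumour necrosis factor alpha, matrix metalloproteinase (MMP)-3"), and a similar list covers oxidative stress.

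Section {20a} sets the level: "For all statistical tests, the significance level is set at" p < 0.05. On scope it says that "the observed outcome parameters (see {12}) serve as the dependent variable". It puts the focus on T0 versus T4 but also plans within-group comparisons and comparisons at the other visits. Section {20b} adds: "Depending on the data and data distribution, subgroup analyses are carried out", with body weight as an example.

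**The concern.** H3, H4 and H5 are each a single statement about a status, but each status is measured by several variables. The article names no key marker, no composite and no required number of significant markers. A flat 5% level on each variable therefore does not say what error rate attaches to the statement itself.

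This matters because the two labels conflict. If H3–H5 are main hypotheses, a reader may take a positive result as confirmed. If the markers are secondary outcomes, the reader should not. The Discussion describes the diet as one that modulates inflammation and oxidative stress favourably, and any such claim from this trial would rest on H4 and H5. A single marker out of six reaching p < 0.05 could be reported as improved inflammation status, and nothing in the text would stop that.

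**Working it through.** **Marker counts, from Outcomes {12}**
- H3: body weight, body fat and waist-to-height ratio (3); plasma lipids (4); carotenoids (4); vitamins D and K (2). 3 + 4 + 4 + 2 = 13. The food record adds at least one more, giving 14.
- H4: 6 inflammation markers.
- H5: ferric reducing ability, malondialdehyde, oxidised glutathione, reduced glutathione and DNA damage = 5.
- H1: one variable (KOOS-QL). H2: one variable (KOOS Symptoms).

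**Level:** 0.05 per test from {20a}. Sidedness is not stated, so two-sided is assumed.

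**Assumption about the decision rule:** one significant marker counts as support. The article does not say this. It is used only to show what the absence of a rule allows.

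**Setting:** the diet has no effect on any marker, with one arm comparison per marker at T4 only.

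Independent markers, either direction: 1 − 0.95^k.
- k = 13: 1 − 0.95^13 = 48.7%
- k = 6: 1 − 0.95^6 = 26.5%
- k = 5: 1 − 0.95^5 = 22.6%

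Independent markers, improvement only. H3–H5 are directional, so a significant worsening is no support, and each marker contributes 0.025: 1 − 0.975^k.
- k = 13: 28.0%
- k = 6: 14.1%
- k = 5: 11.9%

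Correlated markers: equicorrelated normal test statistics, all oriented towards benefit, with critical value 1.96. The document gives no correlations, so a range is shown.

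| Correlation | H3 (13) either / improve | H4 (6) either / improve | H5 (5) either / improve |
|---|---|---|---|
| 0 | 49% / 28% | 26% / 14% | 23% / 12% |
| 0.5 | 33% / 17% | 21% / 10% | 18% / 9% |
| 0.8 | 19% / 10% | 14% / 7% | 13% / 6% |
| One test only | 5% / 2.5% | 5% / 2.5% | 5% / 2.5% |

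Even at correlation 0.8, the improvement-direction rate is about 2.5 to 4 times that of a single test (6.4/2.5 = 2.5 for H5; 9.6/2.5 = 3.8 for H3). Reading the other visits, the within-group tests or subgroups in the same way would raise these rates. By how much is not calculated here, because the number of such tests is not fixed.

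**The case against.** Several points on the other side have weight.

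*A hierarchy already exists.* One primary outcome is named and powered, the research question in {6b} concerns quality of life, and H2 is tied to one subscale. This stands. H1 and H2 are single-variable tests, so a reader who infers that all five hypotheses are inflated goes further than the text allows.

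*The article does not say that one significant marker is enough.* This also stands. A reader might infer that the plan adopts such a rule, and hence that a false claim of improved status has a 20–50% chance. The documents do not support that. The rule is not written, counting both directions overstates support for a hypothesis of improvement, and several H3 markers are linked by construction: α-linolenic and linoleic acid are part of total polyunsaturated fatty acids and also feed the Ω6:Ω3 ratio.

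*Multiplicity for secondary biomarkers is often left to an analysis plan, and adjusted p-values are also compared with 0.05.* This is partly right. A later plan could add an adjustment without contradicting {20a}, and the absence of one is not the point here. What remains is on the page: the same markers serve main hypotheses in {7} and are secondary in {12}, and {20a} applies one level to all of them.

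*The subgroup sentence may mean only that subgroups depend on feasibility.* That reading is open. The sentence sits under additional analyses and is not linked to H1–H5, so it does not show that subgroups will be picked for their results. It does leave their status unstated.

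**Conclusion.** The point holds for H3, H4 and H5, and for interpretation only. The article gives these hypotheses a rank that its own primary outcome, sample size and secondary label do not support, and it fixes a per-test level without saying how several markers settle one hypothesis. If any single significant improvement at T4 were taken as support, the false-positive chance would be 10–28% for H3, 7–14% for H4 and 6–12% for H5, for correlations from 0.8 down to 0, against 2.5% for one test. These figures rest on four assumptions: that decision rule, two-sided 5% tests, equal correlation between markers, and T4 alone. The KOOS-QL result is unaffected. The change should be made, but it does not threaten the trial's main conclusion.

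**What to change.** State that H1 (KOOS-QL, difference between arms at T4, two-sided 5%) is the only confirmatory test, and relabel H2–H5 as secondary. H2 stays on the KOOS Symptoms subscale already named.

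For H3–H5, choose one of two routes before the data are analysed:
- Claim an effect only for markers that are significant at T4 after Holm adjustment across that hypothesis's listed markers. The smallest p-value then faces 0.05/13 = 0.0038 for H3, 0.05/6 = 0.0083 for H4 and 0.05/5 = 0.0100 for H5. The chance of any false positive within a hypothesis is held to at most 5%. If food-record variables belong to H3, list them so that the count is fixed (0.05/14 = 0.0036 with one).
- Or label H3–H5 exploratory and make no efficacy claim from them.

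Report the other visits, the within-group tests and the {20b} subgroups as exploratory, with confidence intervals.

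This changes wording only and needs no further participants or measurements. The price is fewer nominally significant biomarker results.
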